### 3. Study design

This is a multicenter, randomized, three-arm, parallel-group controlled trial that will be conducted at 13 tertiary hospitals in China.

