### **3.1. Randomization and Masking**

An independent third party, the Institute of Basic Research in Clinical Medicine at the China Academy of Chinese Medical Sciences, will generate the randomization sequence and oversee the masking procedures. A stratified block randomization method will be employed, using study center as stratification factors. Random sequences with a block size of 6 will be generated using SAS, version 9.4 (SAS Institute). Allocation concealment will be ensured through a password-protected, central online randomization system. Investigators will be able to access the treatment assignment only after a patient has completed eligibility confirmation and has provided written informed consent.

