## **5. Treatment**

### **5.1. Treatment protocol**

Participants will be randomly assigned in a 1:1:1 ratio to one of three treatment groups: (1) The YBT group: YBT capsules will be administered orally. (2) The LOPM group: LOPM will be performed. (3) The YBT + LOPM group: Participants will receive both YBT capsules and LOPM. In addition to their assigned treatments, all participants will perform standardized lumbar functional exercises throughout the treatment period.

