### 14.2 Allocation of enrolled patients

| Clinical Center                                                 | Number of Patients          |
|-----------------------------------------------------------------|-----------------------------|
| Wangjing Hospital, China Academy of Chinese Medical Sciences    | Total n = 42 (14 per group) |
| Affiliated Hospital of Changchun University of Chinese Medicine | Total n = 33 (11 per group) |
| Affiliated Hospital of Shaanxi University of Chinese Medicine   | Total n = 33 (11 per group) |
| Affiliated Hospital of Shandong First Medical University        | Total n = 33 (11 per group) |
| Dongzhimen Hospital, Beijing University of Chinese Medicine     | Total n = 33 (11 per group) |

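### A single block size of 6, printed in the protocol and applied within each centre, lets site staff who keep a tally deduce up to about 18% of assignments at a 33-patient site

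*Protocol*

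**What the plan says.** Section 3.1 of the protocol sets out the scheme: "A stratified block randomization method will be employed, using study center as stratification factors". The next sentence fixes the block size: "Random sequences with a block size of 6 will be generated using SAS, version 9.4 (SAS Institute". An independent third party generates the lists, and a password-protected central online system conceals them. On release of each allocation it says: "Investigators will be able to access the treatment assignment only after a patient has completed eligibility confirmation and has provided written informed consent".

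Section 3 gives the number of centres ("three-arm, parallel-group controlled trial that will be conducted at 13 tertiary hospitals in China"). Section 5.1 gives the ratio ("Participants will be randomly assigned in a 1:1:1 ratio to one of three treatment groups") and describes the arms: "1) The YBT group: YBT capsules will be administered orally", then "2) The LOPM group: LOPM will be performed", then a third arm that receives both. No placebo capsule or sham manipulation is described. Section 8.1 separates therapists from evaluators and masks the evaluators; no other role is said to be masked.

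Section 14.2 gives twelve of the thirteen centres the target "Total n = 33 (11 per group") and the lead centre 42, or 14 per group.

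**The concern.** Each centre runs its own list in blocks containing two patients per arm. The people delivering treatment see whether a patient receives capsules, manipulation or both. Someone who knows that blocks hold six, and who remembers what has been issued at the centre, can count what is left. Toward the end of a block the next assignment is sometimes known before the next patient has consented.

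What is at stake is selection at entry. Investigators confirm eligibility in person (section 11.5.2). The physician measures the pain VAS mark that must lie from 4 to below 7 (sections 4.2 and 6.1), and some exclusions call for judgement, such as a high risk of bleeding (section 4.3). If the next arm is known, these decisions, or simply the timing of consent, can be influenced by it. The primary outcome is change in a patient-completed disability score at week 2. The baseline covariates listed in section 10.6 would not reliably correct for selection on unrecorded judgement.

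**Working it through.** **Inputs.** Block size 6, strata = centres (section 3.1); ratio 1:1:1, hence 2-2-2 per block (section 5.1); twelve centres of 33 and one of 42 (section 14.2), and 12 × 33 + 42 = 438, which agrees with the stated total.

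**1. Certain assignments in a complete block.** There are 6!/(2!·2!·2!) = 90 distinct orderings. An assignment is certain when only one arm has places left.
- Positions 1 to 4: never certain.
- Position 5: certain when the last two places belong to the same arm. Probability = 3 × C(2,2)/C(6,2) = 3/15 = 0.20.
- Position 6: always certain.

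Expected number per block = 0.20 + 1 = 1.2, and 1.2/6 = 20.0%.

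**2. Over the planned enrolment.** 33/6 = 5.5, so a 33-patient centre uses five full blocks and half of a sixth. The half block adds no certain assignment.
- 33-patient centre: 5 × 1.2 = 6.0 of 33 = 18.2%.
- 42-patient centre: 7 × 1.2 = 8.4 of 42 = 20.0%.
- Whole trial: 12 × 6.0 + 8.4 = 80.4 of 438 = 18.4%.

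**3. Best-guess accuracy.** Someone who always names the arm with most places left is right at positions 1 to 6 with probability 0.333, 0.400, 0.500, 0.533, 0.600 and 1.000. The sum is 3.367, and 3.367/6 = 56.1%. Over 33 patients it is (5 × 3.367 + 1.233)/33 = 54.7%. Chance is 33.3%.

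**4. Under randomly varying sizes.** Blocks of 6, 9 and 12, chosen with equal probability, were simulated over 33 patients. The observer was assumed to know the set of sizes and to update on every assignment; this favours the observer, since the sizes would not be disclosed. Certain assignments fall to about 2%. Best-guess accuracy falls to 51.9%. The share of the excess over chance that remains is (51.9 − 33.3)/(54.7 − 33.3) = 18.6/21.4, or about 87%. So certainty almost disappears, while general predictability hardly moves.

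**5. Site table.** After 30 patients a 33-patient site stands at 10/10/10. The last three come from half a block, and all three arms appear with probability 2·2·2/C(6,3) = 8/20 = 0.40. Otherwise the site ends 12/11/10 in some order. No arm is off by more than one patient at a site. Even if the same arm fell one short at all twelve sites, it would hold 146 − 12 = 134, still above the 133 per group that section 3.2 needs after dropout. The 42-patient centre uses seven full blocks and always ends 14/14/14.

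**The case against.** Fixed permuted blocks within centre, run through a central web system, are a recognised design, and section 3.1 does not contradict itself. Certainty needs someone at the site to know the block size, log every earlier assignment, follow the block boundaries and act on them. The protocol shows none of this happening and gives no distribution list for itself. Recruitment uses posters and social media (section 11.5.1), coordinators do the first screening (11.5.2), 10% of screening is centrally audited, and evaluators are masked (8.1). The remedy also leaves most of the guessing advantage in place.

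Much of this stands as a limit on the size of the point. The 18% is a ceiling under full tracking, no bias in ODI points can be derived from the documents, and the remedy removes certainty rather than predictability. The safeguards do not dispose of it, however. Advertising, coordinator screening and sample audits do not prevent a known next arm from affecting a borderline eligibility call or the day of consent, and evaluator masking addresses assessment rather than entry.

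A reader might infer that a fifth of assignments will in fact be known to staff, or that selection bias is established. The documents support only that such deduction is possible. A reader might also take the mismatch in section 14.2 for a threat to balance or sample size. It is at most one patient per arm per site, and nothing in the protocol makes 11 per group a binding quota.

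**Conclusion.** The point holds as a design weakness worth correcting, not as a demonstrated bias. By printing one fixed block size for centre-level lists, in a trial whose treating staff must know what they give, section 3.1 allows up to 18.2% of assignments at a 33-patient site to be deduced with certainty (20.0% in complete blocks, 18.4% over the planned 438). Central concealment does not prevent this.

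The figures assume 2-2-2 blocks, enrolment at the planned site sizes, and an observer who knows the size and tracks every assignment at the centre. That treating staff are unmasked is itself an inference, from the nature of the arms and from masking being described only for evaluators; the protocol does not use the term open-label.

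The 33-patient targets not being multiples of 6 is an editorial matter with no effect on power or on the conclusions.

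**What to change.** Have the independent unit generate permuted blocks of randomly varying size, for example 6, 9 and 12, for all lists or blocks not yet issued, and hold the sizes there. In section 3.1 replace the stated size with a sentence saying that block sizes vary at random and are not disclosed to sites. In section 14.2 give site totals only, or label the per-group numbers as approximate targets.

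The cost is a regenerated list and small text changes. The downside is slightly looser balance between arms within a site. The protocol should not present the change as making assignments unpredictable: it removes nearly all certain assignments but only a small part of the guessing advantage.

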### **3.2. Sample size**

The sample size was calculated using PASS (Power Analysis and Sample Size), version 11 (Number Cruncher Statistical Systems). The calculation was based on detecting a MCID of 7 points on Oswestry Disability Index (ODI), with a standard deviation of 15.1 points derived from a pre-trial study. A statistical power of 90% and a two-sided alpha of 0.05 were assumed. The calculation was based on the primary objective of demonstrating the superiority of the combination therapy over YBT or LOPM alone, using the Dunnett's test for the two primary comparisons. The initial calculation indicated a requirement of 113 participants per group. After accounting for a 15% dropout rate, the sample size was set at 133 participants per group. To ensure robust multi-center recruitment, the target sample size was further increased to 146 participants per group.

## **4. Study population**

To be enrolled, patients will need to meet all inclusion criteria and none of the exclusion criteria.

### **4.1. Diagnostic criteria**

The diagnosis of LDHR is established based on the clinical guidelines from the North American Spine Society (NASS) and the Chinese Orthopaedic Association (COA).

(1) Medical history: Presence or absence of definitive lumbar injury history.

(2) Symptoms and signs: Low back pain radiating to the buttock and lower extremity, exacerbated by increased abdominal pressure (e.g., coughing, sneezing); Tenderness at the affected vertebral level with radiation to the lower extremity and restricted lumbar mobility; Hypersensitivity or numbness in the affected nerve dermatome; chronic cases may present with muscle atrophy, diminished tendon reflexes, and/or weakened extensor hallucis longus strength.

(3) Physical examination: Motor or sensory deficits in the affected nerve distribution Positive femoral nerve stretch test Positive straight leg raise test (SLRT), positive SLRT reinforcement test, or positive contralateral SLRT.

(4) Imaging findings: MRI-confirmed LDHR at levels consistent with clinical manifestations.

#### **4.2. Inclusion criteria**

- (1) Confirmed diagnosis of LDHR.
- (2) Aged 18-65 years (inclusive).
- (3) Moderate low back or leg pain intensity assessed by visual analog scale (VAS):  $\geq 4$  and  $< 7$ .

#### **4.3. Exclusion criteria**

- (1) History of spinal surgery.
- (2) Spinal compression fractures; lumbar spondylolisthesis grade II or higher; lumbar spondylolysis; lumbar spinal stenosis.
- (3) Spinal tumors; spinal tuberculosis; severe osteoporosis (T-score  $\leq -3.0$  or associated osteoporotic fractures); diabetes with peripheral neuropathy.
- (4) Allergies to non-steroidal drugs, Chinese medicine, or other related medications.
- (5) History of gastrointestinal ulcers/bleeding.
- (6) Patients undergoing coronary artery bypass surgery; those on dual-antiplatelet therapy or with coagulation disorders, or those with a high risk of bleeding.
- (7) Severe skin diseases or skin lesions in the lumbar region.
- (8) Pregnant or breastfeeding women.
- (9) Severe heart failure, stroke, or other severe cardiovascular and cerebrovascular diseases; severe liver or kidney dysfunction.
- (10) Cauda equina injury, lower limb muscle strength  $\leq 3$ , or persistent loss of lower limb motor or sensory function with indications for surgery.
- (11) Special populations who are unsuitable for clinical trials (e.g., blind, deaf, mute, or those with intellectual or mental disorders).

#### **4.4. Drop-out criteria**

Participants who discontinue the study for any reason will be considered dropouts. Voluntary withdrawal will be permitted due to personal reasons, health concerns, or loss of confidence in the study protocol. Investigators will retain the right to withdraw participants for protocol violations, poor compliance, or deteriorating health status that makes continued participation inadvisable. For all dropouts, investigators will perform final safety and efficacy assessments whenever possible and document withdrawal reasons. All data from withdrawn participants will be included in the final intention-to-treat (ITT) analysis to maintain data integrity.

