#### **4.5. Discontinuation criteria**

Participants will be discontinued from the study under any of the following circumstances:

- (1) Adverse event (AE): Discontinuation will be required if a participant experiences:

- 1) A severe allergic reaction (e.g., anaphylaxis, angioedema) deemed related to the study intervention.
- 2) Any other drug-related AE that, in the investigator's judgment, poses a significant health risk or precludes further participation.

(2) Pregnancy: Confirmation of pregnancy during the study period will mandate immediate discontinuation.

(3) Participant Decision: Participants will be able to voluntarily withdraw from the study at any time, for any reason, without prejudice to their future medical care.

(4) Investigator-Initiated Discontinuation: The investigator will be able to discontinue a participant for safety reasons, protocol violations, or administrative necessities.

Procedures Following Discontinuation:

- (1) Upon discontinuation, the investigator will document the primary reason for withdrawal.
- (2) A final safety and efficacy assessment will be performed whenever feasible.
- (3) All discontinued participants will be followed as per protocol, with safety monitoring continuing until any unresolved AEs are resolved or stabilized.

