### **10.6 Statistical method**

The primary efficacy analysis will follow the intention-to-treat (ITT) principle, including all randomly assigned patients. All analyses will be performed using R software, version 4.4.0 (R Foundation for Statistical Computing). Missing data for the longitudinal outcomes will be handled under the assumption of missing at random using multiple imputation. Imputation will be performed using the Multivariate Imputation by Chained Equations (MICE) package in R, generating 5 imputed datasets. The imputation model will include all longitudinal outcome measures from all-time points and all baseline covariates listed above. Results from the imputed datasets will be pooled according to Rubin's rules. Baseline characteristics will be summarized using descriptive statistics. For the continuous outcomes, between-group differences at each specific time point and within-group changes from baseline will be evaluated via pairwise comparisons of the estimated marginal means derived from the linear mixed model (LMM), which will be fitted using the lme4 package (version 1.1.35). These comparisons will be conducted using the emmeans package (version 1.10.0) with Tukey's method for adjustment of P values to control the

family-wise error rate. The model will include fixed effects for treatment group, time (modeled as a categorical factor), and their interaction. The model will be adjusted for the following prespecified baseline covariates: sex, age, body mass index, total duration of lumbar disc disease, duration of the current progressive episode, and degree of herniation at the symptomatic disc level. For categorical outcomes, between-group comparisons will be performed using the chi-square test or Fisher's exact test as appropriate, while the Bonferroni correction will be applied to adjust the significance level and control for type I error arising from multiple comparisons. All statistical tests will be two-sided, with a P value of less than .05 considered statistically significant. Institute of Basic Research in Clinical Medicine, China Academy of Chinese Medical Sciences will perform all statistical analyses.

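### Sections 4.4 and 4.5 do not separate stopping treatment from ending outcome follow-up and differ on what follows withdrawal, which permits avoidable loss of ODI data

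*Protocol*

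**What the plan says.** Section 4.4 gives a single category for everyone who leaves: "Participants who discontinue the study for any reason will be considered dropouts". It then gives the decision partly to the site: "Investigators will retain the right to withdraw participants for protocol violations, poor compliance, or deteriorating health status", with the health ground limited to cases where staying in is inadvisable. What is owed to the analysis afterwards is limited: "For all dropouts, investigators will perform final safety and efficacy assessments whenever possible and document withdrawal reasons". It closes with "All data from withdrawn participants will be included in the final intention-to-treat (ITT) analysis to maintain data integrity".

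Section 4.5 overlaps with this. Its opening line also speaks of discontinuation from the study rather than from treatment. Its investigator-initiated grounds are safety, protocol violations and administrative need; poor compliance is not among them. Its procedures ask, in item (2), for a final assessment where feasible, and then say in item (3): "All discontinued participants will be followed as per protocol", with safety monitoring until open adverse events resolve or stabilise.

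Sections 10 and 10.4 base the primary analysis on all randomised participants. Section 10.6 states: "Missing data for the longitudinal outcomes will be handled under the assumption of missing at random using multiple imputation". The primary outcome in 6.1 is the change in ODI from baseline to week 2, which the study schedule shows as the last visit of the treatment period.

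**The concern.** A site needs one instruction: when a patient stops the assigned treatment, do the scheduled questionnaires go on? Section 4.4 mentions only one last assessment, if it can be had. Section 4.5 item (3) says follow-up continues, but for people it has just described as out of the study. A site that withdraws a patient for poor compliance finds that ground only in 4.4, where no continuing follow-up is stated. With 13 hospitals, different readings are likely.

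The grounds in 4.4 are not neutral. Deteriorating health is close to what ODI measures. Compliance demands differ by arm: capsules three times daily, manipulation three times weekly, or both. Section 7.1 lists worsening back pain and aggravated leg symptoms as manipulation-related events. Under 3.1 investigators can see the assignment after enrolment, and 8.1 masks only the evaluators. Loss under 4.4 could therefore be related to both outcome and arm. An ODI value that was never collected can only be imputed; the promise to keep withdrawn patients' data in the analysis covers what was recorded.

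**Working it through.** **1. The two sections side by side**

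| Point | 4.4 | 4.5 |
|---|---|---|
| What is left | the study | the study |
| Investigator grounds | protocol violation, poor compliance, deteriorating health (qualified) | safety, protocol violation, administrative |
| Final assessment | if possible | if feasible |
| Scheduled follow-up afterwards | not mentioned | continues per protocol, item (3) |

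The final-assessment rule is in effect the same in both. The disagreement is confined to the last row and to poor compliance, which 4.5 does not list. Both sections share the deeper gap: neither distinguishes stopping treatment from ending follow-up.

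**2. Is this a loss of numbers or a risk of bias?**

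Inputs from 3.2: difference 7 points, SD 15.1, power 90%, two-sided alpha 0.05, Dunnett's test for two comparisons, 113 per group, 15% dropout giving 133, target 146.

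- Two-sided Dunnett critical value for two comparisons with a common arm (correlation 0.5): c = 2.212; z for 90% power = 1.282.
- n = 2 × [15.1 × (2.212 + 1.282) / 7]² = 113.6 per group, which agrees with the stated 113 within rounding.
- 113 / (1 − 0.15) = 132.9, that is 133, as stated.
- 146 × 0.85 = 124.1, so about 124 per group remain at 15% loss. Power per comparison is then about 92.5% (89.8% at 113).

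The target absorbs the planned loss of numbers. What remains is bias, which extra patients do not remove.

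**3. Illustrative size of the bias**

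Let p be the share of an arm whose week-2 ODI is lost through withdrawal, and D the amount by which the true values are worse than the imputed ones. An arm mean is then wrong by p × D. With the same D in both arms, the between-group difference is wrong by (pA − pB) × D. The protocol gives neither p nor D, so all values below are assumptions.

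| pA | pB | D (points) | Bias (points) | Share of the 7-point target |
|---|---|---|---|---|
| 8% | 4% | 5 | 0.04 × 5 = 0.2 | 3% |
| 10% | 3% | 10 | 0.07 × 10 = 0.7 | 10% |
| 15% | 5% | 15 | 0.10 × 15 = 1.5 | 21% |
| 15% | 15% | any | 0 | 0% |

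The sign reverses if the other arm loses more patients. For scale, the standard error of a difference with 124 per arm is 15.1 × √(2/124) = 1.92 points, so 0.7 points is about 0.4 standard errors.

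**The case against.** The strongest reply is that the sections can be read as complementary. Section 4.4 never says that follow-up ends; it is silent on later visits, and 4.5 item (3) fills the silence for largely the same people. This stands in part: it rules out saying that 4.4 orders sites to stop collecting ODI. But 4.4 does not refer to 4.5, poor compliance is covered only in 4.4, and 4.5 is unclear in itself, since it has people leave the study and then follows them.

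A reader might also infer that missing at random fails by design. The documents do not support that. Missingness that depends on arm and on recorded outcomes is compatible with the assumption. ODI and VAS are taken at baseline, day 3 and week 1, and 10.6 puts all longitudinal outcomes into the imputation model, so deterioration seen at a visit is observed. What is not recovered is worsening after the last recorded value that the earlier data do not predict. The assumption is at risk, and no more can be said.

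Nor does every withdrawal reach the primary endpoint. Only those in the first 14 days can, and a final assessment in that window may fall close to week 2. Later withdrawals affect the secondary outcomes up to week 26.

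Finally, a reader might infer that the trial becomes underpowered. It does not at the planned 15% loss. Sensitivity analyses may be set out in a statistical analysis plan that is not shown, but no such plan can recover outcomes that were not collected.

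**Conclusion.** The point holds as a defect of instruction to sites. Sections 4.4 and 4.5 leave open whether patients taken off treatment stay in outcome follow-up, and they differ on what comes after withdrawal. This permits, but does not by itself create, avoidable missing outcomes that may be related to prognosis and arm, in a primary analysis that is meant to cover everyone randomised.

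The effect on the result cannot be derived from the documents. The illustration of 0.7 ODI points (0.2 to 1.5) rests wholly on assumed withdrawal shares and shifts, has no known direction, and vanishes if both are equal across arms. The case for change is that the loss is unnecessary: the per-protocol set in 10.5 already deals with major deviations and low compliance, so patients need not leave the study for that purpose.

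**What to change.** Reconcile both sections; amending 4.4 alone would leave the ambiguity inside 4.5.

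- State in 4.4 and 4.5 that non-compliance, a protocol violation or an investigator's decision to stop treatment does not by itself end scheduled outcome follow-up (ODI, VAS, SF-12, and the week-26 MRI where appropriate). Follow-up continues unless the participant withdraws consent or is lost.
- Define dropout as withdrawal of consent or loss to follow-up, and record stopping of treatment separately.
- Do not word the rule so that it requires MRI after a discontinuation for safety or pregnancy.

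The clinical grounds for stopping treatment are not at issue and stay unchanged. The cost is a few sentences and a few more follow-up contacts with patients who have stopped treatment.
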